## Abstract

**Background:**

Allogeneic stem cell transplantation (allo-SCT) is a potentially lifesaving treatment for high-risk hematological malignancy, but survivors experience markedly elevated rates of cardiovascular disease and associated functional impairment. Mounting evidence suggests regular exercise, combined with a reduction in sedentary time through replacement with light exercise may be a useful therapeutic strategy for the prevention of cardiovascular comorbidities. However, this type of intervention has yet to be evaluated in patients undergoing allo-SCT. The ALLO-Active study will evaluate the efficacy of a ~ 4 month multi-faceted exercise intervention, commenced upon admission for allo-SCT, to preserve peak oxygen uptake (VO_2_peak) and peak cardiac output, compared with usual care. The study will also evaluate the effect of the intervention on functional independence, quality of life, and symptoms of fatigue.

**Methods:**

Sixty adults with hematological malignancy scheduled for allo-SCT will be randomly assigned to usual care (*n* = 30) or the exercise and sedentary behaviour intervention (*n* = 30). Participants assigned to the intervention will complete a thrice weekly aerobic and progressive resistance training program and concomitantly aim to reduce daily sedentary time by 30 min with short, frequent, light-intensity exercise bouts. Participants will undergo testing prior to, immediately after inpatient discharge, and 12 weeks after discharge. To address aim 1, VO_2_peak and peak cardiac output (multiple primary outcomes, *p* < 0.025) will be assessed via cardiopulmonary exercise testing and exercise cardiac magnetic resonance imaging, respectively. Secondary outcomes include functional independence (defined as VO_2_peak ≥ 18.mL.kg^−1^.min^−1^), quality of life, and fatigue (assessed via validated questionnaire). Exploratory outcomes will include indices of resting cardiac, vascular, and skeletal muscle structure and function, cardiovascular biomarkers, anxiety and depression, transplant outcomes (e.g., engraftment, graft-versus-host disease), and habitual physical activity, sedentary time, and sleep.

**Discussion:**

Multi-faceted exercise programs are a promising approach for ameliorating the cardiovascular consequences of allo-SCT. If this intervention proves to be effective, it will contribute to the development of evidence-based exercise guidelines for patients undergoing allo-SCT and assist with optimising the balance between acute cancer management and long-term health.

**Trial Registration:**

Australian New Zealand Clinical Trials Registry (ANZCTR), ID: 12619000741189. Registered 17 May 2019.

## Background

Since its inception in 1957, allogeneic stem cell transplantation (allo-SCT) has developed from being an experimental procedure to being the best chance of cure for many high-risk hematological malignancies. Accordingly, the last decade has seen a ~ two-fold increase in the number of allo-SCTs performed globally, and the 5-year overall and progression free survival rates are approaching 62% and 52%, respectively, up from 46% and 42% during 1980–1989 [1, 2]. However, the quality and longevity of survival continues to be compromised by treatment-related cardiovascular adverse effects [3]. Owing to the synergistic effects of toxic anti-cancer therapies [4], prolonged bedrest [5], and the inflammatory perturbations of allografting [6, 7], allo-SCT survivors are susceptible to multi-organ impairment. This has resulted in a population characterised by fatigue [8], poor quality of life [9], reduced muscular strength [10], low aerobic capacity (peak oxygen uptake [VO_2_peak]) [11, 12], and an associated 2-to-fourfold elevation in cardiovascular morbidity and mortality [6, 13–18]. Indeed, in a period of 4–12 weeks (inpatient stay and acute outpatient recovery), allo-SCT recipients experience declines in VO_2_peak approximating the degree of cardiovascular aging typically expected over 2–3 decades [11, 12]. Moreover, as many as 53% of allo-SCT survivors meet criteria for functional disability (VO_2_peak < 18 ml.kg^−1^.min^−1^) [12, 19]—a clinical threshold associated with poorer quality of life and a 7-to-ninefold increased risk of heart failure and all-cause mortality [12, 20]. As such, there is growing interest in therapeutic strategies to reduce cardiovascular risk and improve quality of life in allo-SCT survivors.

Current approaches for mitigating cardiovascular morbidity in patients undergoing allo-SCT include modifications in transplant conditioning intensity and cardiovascular pharmacotherapy. Reduced-intensity transplant conditioning is associated with less cardiac toxicity, although at the cost of higher relapse and graft-versus-host disease (GVHD) rates [21, 22]. Similarly, prophylactic cardioprotective pharmacotherapy can reduce the risk of treatment-related cardiac dysfunction [23], but is not routinely recommended for allo-SCT patients due to concerns surrounding polypharmacy (e.g., increased healthcare costs, adverse drug events and/or drug interactions), overall therapeutic efficacy, and the reality that many patients would be treated unnecessarily [24, 25]. In addition, cardiac-specific pharmacotherapies fail to address impairments in the non-cardiac, ‘peripheral’ (hematological, vascular, skeletal muscle) components of the oxygen transport cascade, which also contribute to the decline in VO_2_peak and cardiovascular health among allo-SCT recipients [26–30].

Combined aerobic and resistance exercise has emerged as a promising preventative therapy for cancer treatment-related cardiovascular dysfunction and functional impairment due to its ability to target the entire spectrum of the oxygen transport cascade. Further, resistance training is an effective tool for stimulating muscle hypertrophy and improving strength—both of which are profoundly impaired among allo-SCT survivors and have been shown to predict poor clinical outcomes [10]. In the context of allo-SCT, aerobic and resistance exercise training has shown promise in improving fatigue [31–34] and quality of life [31, 35, 36], but its efficacy in preserving cardiovascular function is yet to be fully investigated. Indeed, previous randomised controlled trials in allo-SCT recipients have demonstrated favourable effects of combined aerobic and resistance training on indices of aerobic capacity [11, 31, 33, 35–39]—a marker of integrative cardiovascular function strongly associated with cardiovascular and all-cause mortality [19, 40, 41]. However, these trials have relied on indirect estimates of VO_2_peak, with many commencing after the intensive inpatient treatment period wherein cardiovascular insults are arguably greatest, and hence, irreversible cardiovascular impairment may have already occurred. Moreover, the degree to which the beneficial effects on VO_2_peak are mediated by central (cardiac) versus peripheral (hematological, vascular, skeletal muscle) factors remains unknown and is integral to establishing the therapeutic utility of exercise in preventing allo-SCT-induced cardiovascular dysfunction. And finally, none of these trials employed the use of high-intensity interval-based training which has been shown to stimulate a significantly higher improvement in VO_2_peak and overall cardiovascular risk profile compared to moderate-intensity continuous training [42]. Therefore, there is a need for randomised controlled trials—commencing early in the transplant process and including comprehensive cardiovascular evaluation—to determine the efficacy of combined aerobic (moderate-intensity continuous and high-intensity interval) and resistance exercise in preserving the cardiovascular health and functional status of patients undergoing allo-SCT.

Beyond the promotion of purposeful exercise, the reduction and interruption of prolonged periods of time spent sitting or reclining has emerged as an important health target. This is based on the evidence that time spent sedentary poses risks to cardiovascular health that are additional to those of lack of physical activity [43–45]. In the context of allo-SCT, the necessary confinement to a hospital room (~ 3–5 weeks) generally coincides with a marked increase in what is considered an extreme form of sedentary behaviour—bedrest. Thus, a multi-faceted intervention that aims to both increase purposeful exercise and interrupt prolonged periods of sedentary time through replacement with light exercise might be the ideal therapeutic tool to counteract the negative cardiovascular consequences associated with physical deconditioning, cancer therapies, and the pathological perturbations of allografting. Indeed, evidence suggests that structured aerobic and resistance exercise, combined with a reduction in sedentary time, has the potential to have widespread effects on important cardiovascular organs including the heart [46–49], skeletal muscle [50–54], vasculature [47, 55, 56], and blood cells [49], as well as exerting systemic effects that favourably impact these organs [52, 57–60]. No studies have investigated the efficacy of a multi-faceted exercise intervention in preserving cardiovascular function, improving quality of life, and reducing symptoms of fatigue in patients undergoing allo-SCT.

Therefore, in a two-arm randomised controlled trial, the ALLO-Active study will evaluate the efficacy of a ~ 4 month multi-faceted exercise intervention—commenced upon admission for allo-SCT—in preserving cardiovascular function (assessed as VO_2_peak and peak exercise cardiac output; primary endpoints) and improving quality of life, fatigue, and functional independence (VO_2_peak ≥ 18 ml.kg^−1^.min^−1^; secondary endpoints) compared to a usual clinical care control. The intervention is designed to increase purposeful aerobic and resistance exercise and reduce sedentary time through replacement with light exercise and we hypothesise that it will:1. Attenuate the decline in VO_2_peak and peak exercise cardiac output as compared with usual care.2. Improve quality of life, reduce symptoms of fatigue, and improve functional independence compared with usual care.

Exploratory aims include assessing the effect of the intervention on additional *cardiac* factors such as cardiac reserve, cardiac biomarkers, and indices of resting cardiac structure and function, as well as *peripheral* factors including vascular compliance, body composition, indices of skeletal muscle structure and function, metabolic biomarkers, and habitual physical activity, sedentary behaviour, and sleep. This study will also explore the intervention's effect on anxiety and depression and transplant-related variables such as engraftment, immune reconstitution, and GVHD.

## Methods

### Study design

The ALLO-Active trial is a two-arm parallel group, randomised controlled trial in patients with hematological malignancy scheduled to undergo allo-SCT. The purpose of this study is to determine the efficacy of an innovative, individualised multi-faceted exercise intervention delivered during allo-SCT and acute recovery (Phase 1—Inpatient) and the 12 weeks post hospital discharge (Phase 2—Outpatient), compared against a usual clinical care control group (Fig. 1). The study will be conducted at the Baker Heart and Diabetes Institute (BHDI) and Alfred Hospital in Melbourne, Victoria, Australia, and a total of 60 patients will be recruited and randomly allocated to either the exercise & sedentary behaviour (Ex + SED) or Usual Care (UC) arm of the study (*n* = 30 in each). Study assessments will be performed at the BHDI at baseline (~ 2 weeks prior to hospital admission), post-inpatient admission (~ 1 week after inpatient discharge), with final testing to be completed 12 weeks following discharge from inpatient stay.

**Fig. 1 Fig1:**
[figure not shown]
Overview of the ALLO-Active trial design. A comprehensive battery of tests will be conducted in both groups during pre-transplant (baseline) and end of study testing (12-week post-discharge), while an abbreviated version of testing will be performed at post-inpatient testing (detailed in Table 3)

### Ethics

The ALLO-Active trial is registered with the Australian New Zealand Clinical Trials Registry (ANZCTR; registration number: ACTRN12619000741189), funding has been provided via a World Cancer Research Fund International (WCRF) grant (WCRFI 2019–1666) and the protocol has been approved by the Alfred Hospital Human Research Ethics Committee (project number: 134/19). The study team will communicate any important protocol modifications to the trial registry and the Alfred Hospital Human Research Ethics Committee.

### Randomisation

Following completion of baseline testing, participants will be randomly allocated (1:1 ratio) to either the UC or Ex + SED group by an independent researcher via a computer-generated random number sequence. Stratified permuted blocked randomisation will be used with participants stratified by transplant conditioning intensity (myeloablative or reduced intensity conditioning) and sex (male or female). Information relating to the allocation sequence will be kept on a separate, password protected database accessible only to the independent researcher and principle investigator.

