### Blinding

Given the nature of the intervention, it will not be possible to blind participants to their group assignment. The analysis of all outcome measures (e.g., cardiopulmonary exercise test data, echocardiography, cardiac magnetic resonance imaging etc.) will be performed by researchers blinded to participant group assignment and baseline testing values.

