### Participants and recruitment

Participants scheduled to undergo allo-SCT at the Alfred Hospital, Melbourne, Victoria will undergo initial eligibility screening by their nurse transplant coordinator. If identified as interested and eligible based on the criteria outlined in Table 1, the nurse transplant coordinator will provide the participant’s contact details to the ALLO-Active study coordinator. Following further discussion of the purpose of the study and participation requirements via telephone with the ALLO-Active study coordinator, the participant will be provided a participant information and consent form.

**Table 1 Tab1:** Participant eligibility criteria

Inclusion Criteria	Exclusion Criteria
- Age ≥ 18 years	- Unable to communicate or read in English
- Scheduled for allo-SCT	- Contraindications to 3 T MRI (e.g., pacemaker or implanted metallic device)
- Able to exercise at time of enrolment	

After informed consent is acquired, participant demographics, health status, current medications, and cardiovascular risk profile (including family history of CVD, presence of cardiovascular risk factors or overt cardiovascular disease, smoking status, alcohol consumption and menstrual reproductive history) will be documented by questionnaire at baseline. Additional relevant medical history will be extracted from medical records and will include information related to each participants hematological cancer diagnosis, prior anti-cancer treatment history, stem cell transplant conditioning regimen (protocol and dosage [intensity and agents]) and donor (relation, graft source, HLA matching).

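### Giving the principal investigator access to the allocation sequence, with no limit to assignments already made, puts allocation concealment at risk

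*Protocol article*

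**What the plan says.** The Randomisation section sets out three things. The first is who allocates and when: "Following completion of baseline testing, participants will be randomly allocated (1:1 ratio) to either the UC or Ex + SED group by an independent researcher". The second is the method: "Stratified permuted blocked randomisation will be used with participants stratified by transplant conditioning intensity" and by sex, which makes four strata. The third is who can see the sequence information: it is "kept on a separate, password protected database accessible only to the independent researcher and principle investigator". No sentence confines the investigator's access to past assignments.

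Under Participants and recruitment, candidates "will undergo initial eligibility screening by their nurse transplant coordinator", and then discuss the study's purpose and "participation requirements via telephone with the ALLO-Active study coordinator" before they receive the consent form. Table 1 includes the criterion "Able to exercise at time of enrolment", with no threshold attached.

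The Blinding section says that "it will not be possible to blind participants to their group assignment", and that analysis of all outcome measures "will be performed by researchers blinded to participant group assignment and baseline testing values". The limitations paragraph in the Discussion acknowledges the single site, the small sample and the lack of blinding. It does not mention access to the sequence.

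**The concern.** An independent researcher is used so that nobody who runs the trial knows the next assignment before a participant is committed to it. Letting the trial's lead open the same database works against that purpose.

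If the access covers future assignments, and if the investigator can influence who enters or in what order, the next arm in a stratum could be known while entry is still open to judgement. Selection of that kind acts before randomisation, so an intention-to-treat analysis does not correct it. Even if nobody ever used the access, the trial could not easily answer a later charge of foreknowledge, because the written procedure allows it.

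**Working it through.** This is a question of procedure. The plan states no figure on it that could be reproduced, so the check is mainly a comparison of sections.

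**1. Is the access stated or inferred?** It is stated. The Randomisation section names two people with access, and the investigator is one of them. This is a written rule, not a detail that the article leaves to a fuller protocol.

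**2. Does the access reach future assignments?** The wording is open. It refers to information about the sequence in general, which could mean the full list or a record of allocations made. Nothing narrows it to the second meaning.

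**3. Can the person with access affect entry?** The article does not say. Screening belongs to the nurse transplant coordinator and the pre-consent discussion to the study coordinator. Neither is listed as having access. The investigator is neither given a role in eligibility or enrolment nor excluded from one.

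**4. Is there room for foreknowledge to act?** There is some.
- Ability to exercise is a judgement without a stated cut-off.
- Allocation follows baseline testing. That is good practice, but it means that fitness and cardiac results exist before the arm is assigned. For someone who can read the list, the order of allocation within a stratum could then matter.
- The Participant withdrawals section keeps all data collected up to withdrawal, except where withdrawal comes before randomisation. A departure between baseline testing and allocation would therefore not appear in the final analyses.
- The trial is small: 60 participants over 2 × 2 = 4 strata, an average of 60 / 4 = 15 per stratum.

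**5. How much does reading the list add to what could be guessed anyway?** The article gives no block size, so sizes of 2 to 8 are assumed. Take a person who knows the block size and every past assignment in the stratum, and who always guesses the arm with more places left in the block.
- Block of 2: (0.5 + 1) / 2 = 0.75.
- Block of 4: position 1 gives 0.5. Position 2 gives 2/3. Position 3 gives (2/3 × 0.5) + (1/3 × 1) = 2/3. Position 4 gives 1. The mean is 2.833 / 4 = 0.71.
- The same count over all arrangements gives 0.68 for blocks of 6 and 0.67 for blocks of 8.

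A person who can read the list is right 100% of the time, whatever the block size.

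**6. Would the planned analysis repair it?** Only in part. The Statistical analyses section adjusts for baseline values. The Sample size calculation assumes a baseline to follow-up correlation of 0.4, so baseline would account for 0.4² = 0.16, or 16%, of follow-up variance. Imbalance in prognosis that the baseline value does not capture would remain.

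**The case against.** The strongest reply is that concealment fails only when someone who decides or influences entry knows the next assignment, and the article describes no such person. Entry is handled by two coordinators without listed access, and allocation is done by someone independent after baseline testing. Candidates are already scheduled for transplant and are tested about two weeks before admission, so there is limited freedom to re-time them. The article is also a condensed account, and delegation of duties may be set out in the full protocol. All of this stands, and it limits the conclusion to a risk. It does not remove the point, because the access itself is written down without a limit.

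A reader might infer three stronger things that the document does not support:
- **That concealment is defeated.** This needs both access to future assignments and influence over enrolment. The article states neither.
- **That blinded outcome analysis is compromised.** This would require the investigator to analyse outcomes, which the article does not say. The Blinding section already requires analysts who do not know the group.
- **That the bias in the treatment effect can be given a size.** Any such figure would need an invented number of steered patients and an invented prognostic gap between them. The standard deviations in the Sample size calculation support planning of the treatment comparison and do not describe such a gap.

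**Conclusion.** The point holds as a risk to allocation concealment that should be corrected. The protocol article gives the principal investigator access to sequence information without limiting it to past assignments, in a small single-site trial with unblinded participants, permuted blocks in four strata and a judgement-based entry criterion.

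Its effect on the results cannot be quantified from the document. The figures of 67% to 75% against 100% describe predictability only, and rest on assumed block sizes and full knowledge of past assignments. Whether the risk is real in practice depends on two facts that the article leaves open: whether the access covers future assignments, and whether the investigator has any influence on eligibility or the order of entry. The correction is worth making whichever way those facts fall, because it is cheap and removes the question.

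**What to change.** Restrict the sequence to the independent researcher, who releases one assignment at a time, only after the participant is enrolled and baseline testing is complete. The Trial status section says that recruitment was under way at submission. For the recruitment that remains, remove the investigator's access to future assignments, log the date, and report it with the results. If the investigator never had access to future assignments, one sentence should say so.

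If REDCap is used to release assignments, set its permissions so that the study team cannot see the list. The Data management section opens REDCap to study team members, whereas the sequence is now held in a separate database, so a move without that restriction could widen access.

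The cost is a change of permissions and a sentence or two in the protocol. Sample size, alpha, power and the burden on patients are unaffected.

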### Blinding

Given the nature of the intervention, it will not be possible to blind participants to their group assignment. The analysis of all outcome measures (e.g., cardiopulmonary exercise test data, echocardiography, cardiac magnetic resonance imaging etc.) will be performed by researchers blinded to participant group assignment and baseline testing values.

